## Abstract

**Background:**

Coronary heart disease (CHD) and abnormal glucose and lipid metabolism are closely associated and generally coexist. The Qi and Yin deficiency syndrome is a common disease pattern encountered in traditional Chinese medicine. We designed a protocol to determine the effectiveness and safety of Zhenyuan capsules for CHD with abnormal glucose and lipid metabolism.

**Methods:**

This multicenter, randomized, double-blind, parallel-controlled trial was designed in accordance with the CONSORT. We will recruit 200 eligible male patients aged 45–75 years from three participating centers and randomly assign them to treatment and control groups (1 : 1). The primary indicators are glycosylated hemoglobin, fasting blood glucose, 2-hour postprandial blood glucose, and triglyceride levels. The secondary indicators are the Seattle Angina Questionnaire, TCM symptom indicators, ultrasonic cardiography finding, coagulation indicator, and P-selectin level. Measurements will be performed at baseline (T0), the end of the run-in period (T1), and weeks 4 (T2), 8 (T3), and 12 (T4) of the treatment period. Adverse events will be monitored during the trial.

**Discussion:**

This study aims to evaluate the efficacy and safety of Zhenyuan capsules in patients with CHD and abnormal glucose and lipid metabolism. The results will provide critical evidence of the usefulness of the Chinese herbal medicine for CHD with abnormal glucose and lipid metabolism.

**Trial Registration:**

This trial is registered with the Chinese Clinical Trials Registry, with identifier number ChiCTR-TRC-14004639, May 4, 2014.

## 1. Introduction

Treatment of coronary heart disease (CHD), which poses a significant threat worldwide, has made great progress, including thrombolysis, intervention, and coronary artery bypass grafting. However, according to the COURAGE study, these interventional therapies may not effectively reduce the risk of major adverse cardiac events in patients with stable CHD as compared with conservative treatment [1]. Therefore, strengthening drug treatment, controlling cardiovascular risk factors, and lifestyle modification intervention on smoking and exercise are considered the most basic measures.

In addition, diabetes mellitus as an important independent risk factor of cardiovascular disease has been described in the 1999 American Heart Association statement as “a cardiovascular disease” and regarded as a coronary disease equivalent by the National Cholesterol Education Program (NCEP) Adult Treatment Panel III 2001 [2]. In fact, following the growth of living standard, the incidence of type 2 diabetes is increasing yearly. In 2007-2008, the prevalence rates of total diabetes and prediabetes were 9.7% (approximately 92.4 million adults) and 15.5% (approximately 148.2 million adults), respectively [3]. The risk of macroangiopathy increases significantly in diabetes even during the prediabetic state. Fortunately, the 10-year follow-up results of the UK Prospective Diabetes Study showed that patients with intensive glucose control initially showed risk reduction for any diabetes-related end-point by 9% (*P* = 0.04), microvascular disease by 24% (*P* = 0.001), myocardial infarction by 15% (*P* = 0.01), and all-cause mortality by 13% (*P* = 0.007). Moreover, myocardial infarction or all-cause mortality risk was decreased significantly [4]. Thus, early detection and intervention in diabetes are important measures to reduce the morbidity of myocardial infarction and decrease mortality in CHD patients. Glycosylated hemoglobin (HbA1c) level, a test used to monitor the effectiveness of diabetes treatment, is closely related to vascular endothelial injury and coronary atherosclerosis. By measuring HbA1c level, abnormal glucose metabolism can be detected, and then the incidence of CHD can be prevented by controlling glucose levels.

With the publication of the Scandinavian Simvastatin Survival Study, the Cholesterol and Recurrent Events, and other large-scale clinical trials, the relationship between blood lipid levels and cardiovascular atherosclerosis has gradually become clear. Dyslipidemia is closely related to atherosclerosis and is an independent risk factor of CHD. Previous studies showed that lipid lowering can significantly reduce the risk of CHD by 2%, with total cholesterol and low-density lipoprotein cholesterol (LDL-C) both lowered by 1%. Extremely low levels of high-density lipoprotein cholesterol have been shown to increase the risk of CHD by 70% in men and 100% in women. Therefore, controlling abnormalities in serum lipid levels is an important part of the secondary prevention of CHD. The morbidity and mortality of CHD could be significantly reduced by using lipid-lowering drugs, which also could slow down and reverse the progression of atherosclerosis.

Furthermore, dyslipidemia, which is associated with diabetes, is the main cause and one of the major risk factors of diabetes-associated macrovascular complications [5]. Owing to the abnormally elevated lipids deposited in the cell and vessel wall by some mechanisms, atherosclerotic plaques are formed, and, finally, stenosis, even occlusion, occurs in the blood vessel lumen. According to NCEP, diabetes has a high risk of developing into CHD within 10 years. The primary preventive goal is to reduce the LDL-C level [6]. Moreover, CHD with diabetes may occur with a more serious lipid metabolism disorder. For these reasons, more attention should be paid to the treatment of dyslipidemia and diabetes in CHD patients.

Traditional Chinese medicine (TCM) emphasizes symptomatic treatment and has long-term application in CHD-related diseases. From the view of TCM, patients with CHD and abnormal glucose and lipid metabolism can be divided according to symptoms. A common symptom is the Qi and Yin deficiency syndrome. The effect of Zhenyuan capsules in the treatment of this type of patients has been observed in the clinical setting. The main component of the Zhenyuan capsule is ginseng fruit saponin (GFS), a ginsenoside extract from the mature fruit of the* Panax ginseng *fruit. Previous studies showed multiple components of saponin in GFS, such as ginsenosides Re, Rb1, Rb2, Rc, Rg1, Rg2, and Rd. The structures of these compounds are identified on the basis of physicochemical constants, ultraviolet light, nuclear magnetic resonance, and spectral analysis. The study by Xu et al. [7] showed that the main component of GFS is ginsenoside Re, which accounts for as much as 85% of the GFS content, 30 times higher than the content in ginseng roots and 6% in all ginseng. The remainder is a small amount of ginsenoside Rg2 and trace amounts of ginsenoside Rg1. This means that ginsenoside Re may be the main active constituent. In addition, modern pharmacological studies have shown that GFS has the effect of lowering blood pressure and blood glucose level, countering arrhythmias, protecting against myocardial ischemia-reperfusion injury, and other actions.

Therefore, we designed this randomized, double-blind, parallel-controlled, multicenter, phase IV clinical trial to investigate the efficacy of the Zhenyuan capsule in the treatment of CHD accompanied with glucose and lipid metabolic disorders. The outcome measures are focused on symptom reduction and improvement in physiochemical indexes. We will also determine clinical safety.

## 2. Methods/Design

### 2.1. Study Design

This study is registered with the Chinese Clinical Trial Registry (registration number ChiCTR-TRC-14004639). The multicenter, randomized, double-blind, parallel-controlled, phase IV clinical study follows the recommendations of the CONSORT [8] and SPIRIT statements [9]. This study is financially supported by Jilin Jian Yisheng Pharmaceutical Co. Ltd., Jilin, China. The company is not involved in the clinical trial design, data collection and analysis, or other parts of the study.

Participants will be recruited from three participating centers, namely, Xiyuan Hospital of China Academy of Chinese Medical Sciences, Guan'anmen Hospital of China Academy of Chinese Medical Sciences, and the Second Affiliated Hospital of Tianjin University of TCM. The leading unit among the three centers is Xiyuan Hospital. In this trial, 200 patients will be recruited and randomly allocated to two groups (treatment group, *n* = 100; control group, *n* = 100). Clinical assessment will be performed at baseline (T0, 2 weeks preceding the treatment) and at the end of the 2-week run-in period (T1). Participants will then receive the treatment for 12 weeks. In the treatment period, the intervention assessments are performed at weeks 4 (T2), 8 (T3), and 12 (T4).  Figure 1 shows the study procedures.

### 2.2. Participants

Inpatients and outpatients will be screened and identified in three participating centers strictly according to the inclusion and exclusion criteria. Written informed consent of each participating patient is required for entry to the study.

#### 2.2.1. Inclusion Criteria

Subjects are eligible for study participation if they meet the following criteria: (1) coronary angiography or coronary computed tomographic angiography shows that at least one of the main branches of the coronary artery has stenosis of at least 50%; (2) TG levels between 1.70 and 2.25 mmol/L and HbA1c level between 5.7% and 7%; (3) the TCM syndrome differentiation is Qi and Yin deficiency; (4) age between 45 and 75 years at screening; and (5) providing informed consent form.

#### 2.2.2. Exclusion Criteria

Participants will be excluded if they report any of the following criteria: (1) serious cardiovascular diseases, including severe valvular heart disease, heart valve replacement, refractory heart failure, cardiac function grade IV (NYHA), and cardiogenic shock or serious cardiac insufficiency (EF < 35%); (2) mental disease or malignant tumor; (3) renal insufficiency, serum creatinine level of >2.5 mg/dl for men (>220 *μ*mol/l) and >2.0 mg/dl (>175 *μ*mol/l) for women; (4) hypohepatia, liver enzyme level of >2 times the normal value; (5) high risks of hemorrhage, hemophilia, and platelet dysfunction, or history of thrombocytopenia, which might influence the use of antiplatelet drugs; (6) active or emerging (<3 months) bleeding, including gastrointestinal bleeding, stool occult blood, or gross hematuria; (7) pregnant or attempting to become pregnant; (8) allergic constitution; (9) joined another trial or received random allocation in another study within the past 3 months; or (10) being unable or unwilling to sign the informed consent form, being noncompliant, or having poor possibility of a follow-up visit.

#### 2.2.3. Withdrawal, Dropout, and Discontinuation

Participation will be discontinued if the participant has sudden worsening of condition that is not confirmed to be associated with this trial, or serious adverse events, or is unable to cooperate with the trial investigators and/or to complete the follow-up. If the condition continues to worsen, complications or special physiological changes emerge, a participant refuses to continue the trial, or a participant uses medicines that are not permitted in this trial, the patient will be withdrawn from the trial after the researcher's assessment. The data will be considered invalid but will still be included in the full analysis set (FAS). Information from dropouts will be collected by phone interviews, such as the reason for the trial discontinuation and the status of the final medication received. Participants who withdraw from the trial will receive appropriate treatment for adverse events.

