### 2.3. Intervention

Patients who meet all the inclusion and none of the exclusion criteria will be randomized into two groups as follows: (1) treatment group, 0.5 g of Zhenyuan capsule, 3 times/day, and (2) control group, 0.5 g of placebo, 3 times/day. According to the Guideline for the Diagnosis and Treatment of Chronic Stable Angina, participants can maintain the conventional drug treatments such as antiplatelet agents, statins, nitrates, anticoagulation drugs, *β*-blockers, calcium channel antagonists, angiotensin-converting enzyme inhibitors, or angiotensin II receptor antagonists. However, statins are the only Western medicine for lipid treatment. Patients diagnosed as having type 2 diabetes maintain the current Western medicines for hypoglycemic effects. To avoid discussing their medications among themselves, participants are advised to take the drugs at home and required to remain isolated from each other. In addition, the treatment allocation remains blind throughout the study. Participants will not be permitted to use other treatments for angina pectoris in CHD and diabetes, including TCM herbs and Chinese patent medicine. In the run-in period, any TCM medications for improving blood lipid or glucose levels will not be permitted.

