### 2.4. Outcomes and Measures

The primary indicators, HbA1c, fasting blood glucose (FBG), 2-hour postprandial blood glucose (2hPBG), and triglyceride (TG) levels, will be tested at T0, T1, T2, T3, and T4. The secondary indicators, ultrasonic cardiography (UCG) finding, coagulation indicator, and P- selectin level, will be assessed at T1 and T4. Cardiac death, nonfatal myocardial infarction, coronary revascularization, Seattle Angina Questionnaire (SAQ) score, and TCM symptom indicators will also be monitored periodically. Adverse events, which include hemorrhage, will be followed up using electrocardiography, routine urinalysis, routine stool test, and liver and kidney function tests (ALT, AST, Cr, and BUN) from T1 to T4. Items to be measured and the time window of data collection are shown in Table 1.

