### 2.10. Statistical Analyses

Statistical analyses will be conducted by an independent statistician from Xiyuan Hospital. In the FAS, patients will be dosed with the study drugs at least one time and one clinical observation will be recorded. Participants with good compliance and without any protocol deviations will be included in the per-protocol set (PPS). Subjects with safety data who have completed at least one study visit will be included in the safety analysis. The mean ± SD will be used in continuous variables. The characteristic comparability between the two groups will be evaluated by a two-sample Student *t*-test for continuous variables and the Fisher exact test or *χ*^2^ test for categorical variables. In this multicenter trial, the Cochran-Mantel-Haenszel test and the analysis of variance will be used. For diminishing the influence of confounding factors on the curative effect, analysis of covariance and the logistic regression model will be applied. For all the analyses, the difference with a value of *P* < 0.05 will be statistically significant. All analyses will be conducted using the SAS software version 9.3 (SAS Institute, Cary, NC, USA).

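### Patients who take a non-permitted medicine are withdrawn and their data called invalid, so later laboratory values can be lost for reasons linked to the outcome

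*Protocol article*

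**What the plan says.** Section 2.2.3 of the protocol article lists use of a non-permitted medicine among the reasons for leaving the trial: if "a participant uses medicines that are not permitted in this trial, the patient will be withdrawn from the trial after the researcher's assessment". Continued worsening is another reason in the same sentence. On the data, it says "The data will be considered invalid but will still be included in the full analysis set (FAS"). On later contact, it says "Information from dropouts will be collected by phone interviews, such as the reason for the trial discontinuation", together with the final medication status. It describes no laboratory visit after withdrawal.

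Section 2.3 sets what is permitted. "Patients diagnosed as having type 2 diabetes maintain the current Western medicines for hypoglycemic effects", and "Participants will not be permitted to use other treatments for angina pectoris in CHD and diabetes, including TCM herbs and Chinese patent medicine".

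Section 2.4 names HbA1c, fasting glucose, 2-hour glucose and triglycerides as primary indicators, which "will be tested at T0, T1, T2, T3, and T4".

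Section 2.10 defines the FAS by the condition that "patients will be dosed with the study drugs at least one time and one clinical observation will be recorded". It defines a separate per-protocol set: "Participants with good compliance and without any protocol deviations will be included in the per-protocol set (PPS").

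**The concern.** The rule ends trial participation, not just use of the capsule, and the event that triggers it can be a result of the outcome. A diabetic patient whose glucose is poor at T2 or T3 may be given a new glucose-lowering drug. That drug is not a current medicine, so the patient can be withdrawn and the T4 blood sample is not taken. If the capsule lowers glucose, this happens less often on the capsule than on placebo. The patients who reach T4 are then no longer comparable between arms.

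FAS membership does not repair this. It requires one dose and one observation, so the patient is counted but the later values are still absent. Calling the data invalid while keeping the patient in the FAS also gives the analyst conflicting instructions about values that were collected. The FAS result then depends on how that conflict is settled: some methods understate the effect and others overstate it.

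The withdrawal is not needed to protect the per-protocol analysis, because section 2.10 already removes protocol deviations from that set.

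**Working it through.** No figure in the protocol is disputed on this point. The question is how much the rule could matter, and the documents give no rate of added treatment, no SD and no correlation. What follows is an illustration under stated assumptions.

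**From the documents:** 100 patients per arm (section 2.1), significance level 0.05 (sections 2.9 and 2.10, taken as two-sided), primary laboratory values at T2, T3 and T4 (section 2.4).

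**Assumed:** X is the T2/T3 value and Y the T4 value of the laboratory variable that prompts the added drug. Both have SD 1 and correlation r of 0.5 to 0.8. The control mean is 0 and the treated mean is −D. A patient is withdrawn if X exceeds z, where z is set so that a proportion c of controls (5%, 10% or 20%) exceeds it.

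**Choice of D.** The difference detectable with 80% power is (1.96 + 0.84) × √(2/100) = 0.396 SD, so D = 0.4 is used. With complete data, power at D = 0.4 is 0.807.

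**Formulas** (φ and Φ are the standard normal density and distribution function):

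- Withdrawal on the capsule: 1 − Φ(z + D).
- Understatement when only observed T4 values are analysed: r × [φ(z)/Φ(z) − φ(z+D)/Φ(z+D)].
- Overstatement when the last value is carried forward: (1 − r) × [φ(z) − φ(z+D)].
- Power for observed T4 values: normal test using the reduced effect, the reduced numbers and the truncated variances.

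**Example, c = 10%.** Here z = 1.282.

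- Capsule withdrawal is 1 − Φ(1.682) = 4.6%.
- The ratios φ/Φ are 0.1755/0.90 = 0.195 for control and 0.0970/0.9537 = 0.1017 for capsule, a difference of 0.0933.
- The understatement is 0.5 × 0.0933 = 0.047 SD, or 0.8 × 0.0933 = 0.075 SD.
- Carrying forward overstates by 0.5 × (0.1755 − 0.0970) = 0.039 SD, or 0.2 × 0.0785 = 0.016 SD.

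**Results at D = 0.4** (each pair is r = 0.5 / r = 0.8):

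| Withdrawn, control vs capsule | Understatement, observed T4 only (SD) | Power, observed T4 only | Overstatement, last value carried forward (SD) |
|---|---|---|---|
| 5% vs 2.0% | 0.029 / 0.047 | 0.747 / 0.732 | 0.027 / 0.011 |
| 10% vs 4.6% | 0.047 / 0.075 | 0.698 / 0.671 | 0.039 / 0.016 |
| 20% vs 10.7% | 0.072 / 0.115 | 0.609 / 0.561 | 0.048 / 0.019 |

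As a share of the true effect, the understatement runs from 0.029/0.4 = 7% to 0.115/0.4 = 29%. With D = 0.2 it is 0.017 to 0.062 SD. With D = 0 both arms lose the same proportion and the bias is 0. A simulation with 4 million patients per arm at c = 10%, r = 0.8 gave effects of 0.326 SD (observed only) and 0.416 SD (carried forward), against 0.325 and 0.416 from the formulas.

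**If visits are kept instead.** The added drug then acts on the retained values. At 10% vs 4.6% use, the arms differ by 5.4 percentage points.

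- If the drug lowers the outcome by 0.5 SD, the effect seen is 0.4 − 0.054 × 0.5 = 0.373 SD, power 0.751.
- If it lowers it by 1 SD, the effect seen is 0.4 − 0.054 × 1 = 0.346 SD, power 0.688.

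**The case against.** The strongest objection is that the remedy gains little power. At 10% vs 4.6% withdrawal and r = 0.5, analysing observed values leaves 0.4 − 0.047 = 0.353 SD with power 0.698. Keeping the visits gives 0.346 SD and 0.688 if the added drug has a 1 SD effect, which is no better. This stands as arithmetic. It does not defeat the change, whose main gain is that every patient has measured outcomes and is analysed as randomised. Other ways of handling added treatment stay open once the values exist. With no capsule effect the model shows no bias, so it gives no argument about false positives.

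The assumed rates may also be high. Patients enter with HbA1c of 5.7% to 7%, keep their current drugs and are treated for 12 weeks. Withdrawal follows the researcher's assessment, so it is not automatic, and 20% equals the whole allowance for loss in section 2.9. The 5% row is the more cautious guide, and the 29% and 56% figures come only from the extreme corner.

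The angina route is weaker. A new anti-anginal drug is a trigger only if permission to maintain conventional drugs is read strictly, and withdrawal for angina selects less directly on a laboratory value. At an assumed r of 0.1 to 0.2 the 10% case gives 0.1 × 0.0933 to 0.2 × 0.0933, about 0.01 to 0.02 SD. Likewise, withdrawal for glucose does not select directly on triglycerides.

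Finally, invalid may simply mean not valid for the per-protocol set, and this is a condensed article whose full protocol and SAP may say more. The harmless reading is possible, but the text does not state it. An SAP can choose how to treat missing values; it cannot recover blood samples that were never drawn. In this model a longitudinal analysis using T2 and T3 values could remove much of the bias, but only if those values are not set aside as invalid.

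**Conclusion.** The concern holds. The protocol article itself fixes withdrawal from the trial, the label invalid alongside FAS membership, and phone contact as the only described follow-up. Together with the bar on other diabetes treatments, these rules allow scheduled laboratory values to be lost for a reason tied to the outcome.

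Size and direction cannot be derived from the documents. Under the assumptions above, with a true effect of 0.4 SD, the estimate could be 0.03 to 0.12 SD too small if only observed week-12 values are used, or 0.01 to 0.05 SD too large if the last value is carried forward. The figures apply to a laboratory trigger acting on the same variable, an unadjusted comparison and a sharp withdrawal threshold. With no capsule effect, only precision suffers. The change should be made because it is cheap and the lost values cannot be recovered later. Confidence is medium.

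**What to change.** Amend section 2.2.3 as follows:

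- Record use of an added anti-anginal, glucose-lowering or other non-permitted treatment as a protocol deviation. It affects the per-protocol set only and does not by itself end participation.
- Keep the scheduled T2 to T4 measurements, treat those data as valid (deleting the statement that they are invalid), and analyse the patient in the randomised arm in the FAS.
- Where worsening requires the capsule to be stopped, stop the capsule but keep the visits if the patient agrees.
- Report added treatment by arm, using the concomitant-medication records already in Table 1.

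In the same amendment, state in section 2.3 whether starting or increasing one of the listed conventional drugs is permitted. That clinical choice is the sponsor's.

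The cost is a wording change to two sections and one descriptive table, with no extra patients and no visits or tests beyond Table 1. The downside is that retained outcomes include the effect of the added drug. At 10% vs 4.6% added use and a drug effect of 0.5 to 1 SD, this dilutes the contrast by 0.03 to 0.05 SD.

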### 2.6. Study-Specific Visits and Procedures

Table 1 shows the study-related procedures. All eligible patients should have a 2-week run-in period followed by the treatment period. Participants are assessed by the same researcher consistently throughout the trial. Baseline measures include demographic data; medical and treatment history; medications; vital signs (temperature, breathing, heart rate, and blood pressure); FBG, 2hPDG, HbA1c, and TG levels; and liver and kidney function tests. Baseline measurements will be repeated with all participants at T1 and T4. The TCM syndrome indicators, SAQ, adverse events, and outcome measures will be recorded from T1 to T4.

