## Figures and Tables

**Figure 1 fig1:**
[figure not shown]
Study flowchart.

**Table 1 tab1:** Measurement items and time points for data collection.

	Screening	Treatment period			
	T0	Run-in period (T1)	Week 4 (T2)	Week 8 (T3)	Week 12 (T4)
*Basic medical history recording*					
Informed consent	×				
Inclusion/exclusion criteria		×			
Demographic data		×			
Medical and treatment history recording		×			
Complication and symptom recording		×			
Concomitant medication		×	×	×	×
Vital signs		×	×	×	×
*Efficacy observation*					
TG, FBG, 2hPBG, and HbA1c levels	×	×	×	×	×
TCM symptom indicators		×	×	×	×
Seattle Angina Questionnaire score		×	×	×	×
Coagulation indicator		×	×	×	×
P-selectin level		×	×	×	×
Angina pectoris scores and end-point event		×	×	×	×
ECG		×			×
UCG		×			×
*Safety assessment*					
Liver and renal function tests	×	×	×	×	×
Hemorrhage		×	×	×	×
Routine blood and urine tests		×			×
Routine stool and occult blood tests		×			×
*Other works*					
Randomization and allocation		×			
Drug distribution		×	×	×	
Medicine recycling and drug quantity statistics			×	×	×

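### Leaving the trial for worsening or a serious event also ends visit-based recording of cardiac events, and follow-up of those events to week 12 is not secured

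*Protocol article*

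**What the plan says.** The protocol article describes exit in section 2.2.3. Serious adverse events are the second trigger in this sentence, which is cut short here: "Participation will be discontinued if the participant has sudden worsening of condition that is not confirmed to be associated with this trial, or serious adverse". For continuing worsening, complications, refusal or use of medicines that are not permitted, "the patient will be withdrawn from the trial after the researcher's assessment". Both rules concern the trial as a whole. Nothing separates stopping the capsule from stopping follow-up. The same section calls the data of such patients invalid yet keeps them in the full analysis set.

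Contact after exit is described in one sentence: "Information from dropouts will be collected by phone interviews, such as the reason for the trial discontinuation", with the status of the final medication as the other item.

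On the events themselves, section 2.4 states: "Cardiac death, nonfatal myocardial infarction, coronary revascularization, Seattle Angina Questionnaire (SAQ) score, and TCM symptom indicators will also be monitored periodically". Section 2.6 adds: "The TCM syndrome indicators, SAQ, adverse events, and outcome measures will be recorded from T1 to T4". Table 1 has a row headed "Angina pectoris scores and end-point event", marked at T1, T2, T3 and T4. Randomisation is also placed at T1, so T4 is 12 weeks after randomisation.

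**The concern.** The conditions that end participation overlap with the cardiac events being monitored, or may come before them. Event recording is tied to visits, and a patient whose participation has ended has no further visits. If the rule is followed as written, systematic recording stops early in patients who worsen and runs to week 12 in those who stay well.

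Loss of follow-up of this kind is informative because it depends on clinical course. If the two arms differed in how often patients worsen, they would also differ in how long events are looked for. The article sets out to evaluate safety as well as efficacy, and in 100 patients per arm over 12 weeks the event counts may be small, so a few unrecorded events could change how they read.

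**Working it through.** **1. What each passage requires**

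| Place | Rule | Consequence for a patient who leaves early |
|---|---|---|
| 2.2.3 | Participation ends on sudden worsening or a serious adverse event; withdrawal from the trial for continuing worsening, complications, refusal or non-permitted medicines | No later visits |
| 2.4, 2.6, Table 1 | Cardiac events recorded at T1 to T4 | Later recording has no visit to attach to |
| 2.2.3, phone interview | Two example items: reason for leaving, status of final medication | Neither asks about events after exit |

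**2. Which events are at risk**

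- *The exit is caused by a monitored event.* A nonfatal infarction would ordinarily be a serious adverse event, although the article does not define the term. That infarction is captured: it is monitored under 2.4, and section 2.5 requires severe adverse events to be reported within 24 hours. In a count of patients with at least one event, this patient is already counted. Only a later event, such as a cardiac death after the infarction, may be missed.
- *The exit is caused by worsening or by another serious event.* A first infarction, revascularisation or cardiac death after exit may be missed. For example, a patient leaves at week 5 and has an infarction at week 6. T3 (week 8) and T4 (week 12) do not take place for this patient. This loss is related to clinical course.
- *The exit has another cause*, such as refusal or a non-permitted medicine. A first event after exit may be missed, but the link with clinical course is weaker or absent.

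**3. Size**

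The documents give no rate of serious adverse events or of cardiac events, so no size can be derived from them. The nearest figure is the 20% allowance for loss in section 2.9. Applied to 200 patients it gives 0.20 × 200 = 40, but it is not split by reason.

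An illustration on assumptions only:

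expected missed events = 200 × (share leaving on a serious event) × (risk of a later monitored event by week 12)

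| Assumed share leaving | Patients leaving | Later risk 2% | Later risk 10% | Later risk 20% |
|---|---|---|---|---|
| 2% | 4 | 0.08 | 0.4 | 0.8 |
| 5% | 10 | 0.2 | 1.0 | 2.0 |
| 10% | 20 | 0.4 | 2.0 | 4.0 |

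The range is about 0.1 to 4 events in total over both arms. If departures fall on average at mid-treatment, the person-time lost is half the share leaving, 1% to 5%. Nothing in the documents says how missed events would divide between the arms.

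**4. Sample size**

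The planned 25 per group rests on relief of angina symptoms (94% against 64%). The unpooled formula in section 2.9, with two-sided α = 0.05 and 80% power, gives (0.94 × 0.06 + 0.64 × 0.36) / 0.30² × (1.960 + 0.842)² = 25.01, which agrees with the stated 25. Cardiac events do not enter it, so this point leaves it unchanged.

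**The case against.** A reader might infer that the call covers nothing but the reason and the last medication, and that later events are therefore not counted. The documents do not support this. The call is described with examples, "such as the reason for the trial discontinuation and the status of the final medication received", which is not a closed list, and asking why a patient stopped could bring out an infarction or a death. No passage says that events after exit are left out, and Table 1 makes no exception for dropouts.

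A reader might also infer that the comparison of the arms is biased, or that missed events could match those recorded. That would need event rates and a difference in exits between the arms, and the documents give neither.

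Two further points reduce the weight. The three cardiac events are not among the four primary indicators or in the abstract's list of secondary indicators, and the article plans no between-group test of them. An article also condenses its protocol, and a full phone script would not be expected in it.

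All of this stands as a limit on the claim, but it does not remove the point. The article is not merely silent: it states that participation ends, and that rule does not fit its own schedule of event recording to T4. If later events are never collected, an analysis plan cannot recover them.

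**Conclusion.** The point holds in limited form. As written, section 2.2.3 ends visit-based event recording for patients who worsen or have a serious event, and nothing in the article secures follow-up of cardiac death, infarction and revascularisation to week 12 for them. Later events may be missed; it is not established that they will be. The triggering event is not lost.

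The size is unknown. The range of about 0.1 to 4 events rests wholly on assumed exit shares of 2% to 10% and assumed later risks of 2% to 20%. The conclusion also assumes that ending participation means no further study visits, which is the plain reading of 2.2.3. The definitions of the primary indicators and the sample size are not affected. This is an inexpensive improvement worth making, and it does not threaten the main comparison.

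**What to change.** Reconcile section 2.2.3 with 2.4, 2.6 and Table 1 by separating the end of treatment and visits from the end of event ascertainment:

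- State that cardiac death, nonfatal infarction and coronary revascularisation are recorded to week 12 after randomisation for every randomised patient who has not withdrawn consent.
- Add these three events to the phone interview already planned, and make one call at the patient's week-12 date.
- Count the events in the arm to which the patient was randomised.

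The rules on when treatment stops stay as they are. The cost is three questions and one call for each early leaver, which takes a little site time and needs no extra procedure.
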